## Abstract

Work-related stress presents a significant impact on work performance and physical health. It has been associated with the onset of a multitude of symptoms that can lead to occupational stress diseases, namely Adjustment Disorder and Post-Traumatic Stress Disorder. The literature has evidenced that “exposure therapy” of cognitive-behavioral training (CBT-E) seems to be the most effective technique to manage stress symptoms, including work stress diseases, and several studies have considered Virtual Reality (VR) as an adjuvant tool to exposure-based psychotherapy (CBT-VR) for the treatment of multiple psychiatric disorders. The aim of this study is to evaluate the effectiveness of CBT with exposure to stressful work scenarios in imaginative (CBT-E) and in immersive virtual reality (CBT-VR) scenarios in a group of workers affected by work-related stress disorders and compare the clinical and physiological outcomes between the two exposure techniques. A long-term goal would be to develop an evidence-based rehabilitation program as a treatment for the reintegration into work of patients affected by these psychiatric disorders.

## 1. Introduction

### 1.1. State of the Art and Rationale of the Study

According to a definition provided by the National Institute for Occupational Safety and Health, work-related stress can be defined as “harmful physical and emotional responses that occur when the requirements of the job do not match the capabilities, resources, or needs of the worker. Work-related stress can adversely affect health and even lead to injury” [1]. In Europe, 147 million workers reported that they work very tight schedules and are required to meet pressing deadlines [2,3,4]. Work-related stress affects about 22% of workers in Europe. In Italy, the number is 27%. Overall, 50% of working days lost in a year are related to work-related stress. The European Union has estimated the economic cost of work-related stress to be approximately EUR 265 billion per year [5,6].

The studies conducted so far on the factors of one’s working environment that generate stress have dealt with a complex reality that is difficult to break down into its specific features [7,8,9]. In the 1970s, Karasek’s “job strain” model stated that the greatest risk to physical and mental health from stress occurs in workers facing high psychological workload demands or pressures combined with low control or decision latitude in meeting those demands [9,10]. In 1991, Kasl produced an analytical list of the different aspects of work involved in the production of emotional distress and stress. Work stress can be caused by different factors, such as the content of the work, its organization, the environment, poor communication, etc. [11]. In October 2004, the four major European organizations in the field (the European Trade Union Confederation (ETUC), Union of Industrial and Employers’ Confederations of Europe (UNICE), European Association of Craft, Small and Medium-sized Enterprises (UEAPME), and Centre of Employers and Enterprises providing Public services (CEEP) signed an agreement on the significance of work-related stress, the policies to prevent it, and the psychiatric diseases derived from it (European Agreement on Work-Related Stress, Brussels, 2004) [12].

What has emerged to date is that work-related stress disorders are the diseases in which occupational factors interact with non-occupational factors and individual conditions [13]. Consistently, in the presence of a worker with anxiety and/or mood symptoms related to work problems, it is necessary to carry out a careful multidisciplinary evaluation of the organization of work, the personal global functioning, and personality traits aimed at recognizing the eventuality of an occupational disease due to work-related stress, such as Adjustment Disorder (AD) or Post Traumatic Stress Disorder (PTSD). The first occurs in response to one or more non-extreme stressors, while the second represents the response that may occurs in people who have experienced or witnessed a life-threatening traumatic event or a catastrophic situation [14,15,16,17].

AD is a frequent diagnosis among workers and is characterized by heterogeneous emotional or behavioral (but also somatic) symptoms, related to traumatic and stressful events, which arise in the three months following one or more work stressful events or organizational conditions. Once the stressor has terminated, the symptoms may resolve within six months (Acute Adjustment Disorder) or may persist for a longer period if the stressor has long-term consequences. Workplace exposure to serious traumatic events can also cause PTSD, a clinical condition characterized by more specific symptoms of re-experiencing, avoidance, hyperarousal, and negative alterations of cognition and mood in relation to traumatic events [18]. 

Randomized controlled trials regarding interventions aimed at reducing work-related stress indicate that cognitive behavioral therapy (CBT) is more effective than other interventions [19,20]. Throughout the literature, CBT-based interventions have been effective in improving the perceived quality of working life, improving psychological resources and responses, reducing distress, decreasing perceived stress, and decreasing symptoms of anxiety and depression [21,22]. CBT is a type of psychotherapeutic treatment that helps people to identify and change destructive or disturbing thought patterns that have a negative influence on their behavior and emotions. Under stressful conditions, some individuals tend to feel pessimistic and unable to solve problems. CBT promotes more balanced thinking to improve the ability to cope with stress [23]. These CBT interventions typically range from hours-long workshops to year-long interventions [24,25]. Van der Klink’s group (2001) [26] found an inverse relationship between the number of sessions and the effect size of CBT. This was reported in a quantitative meta-analysis evaluating 48 experimental studies. Ulter, Richardson, and Rothstein (2008) [24] have suggested that shorter programs may be more practical and cheaper to implement than longer ones. 

The literature has evidenced that “exposure therapy” of CBT (CBT-E) seems to be the most effective technique to manage stress symptoms, including work stress diseases [27]. The overall goal of exposure therapy, according to the American Psychiatric Association, is to “reduce a patient’s fear and decrease avoidance” of a patient to his “feared objects, activities, or situations” using a safe environment [28]. There are many different approaches to exposure therapy, which incorporates relaxation exercises as well as gradual exposure to the feared item or situation which tackles the person’s milder fears first before working on the more difficult tasks. In certain situations, the “flooding technique” of exposure therapy (as opposed to a gradual approach) is used to treat the most difficult or intense fear or phobia, with therapy continuing until that fear or phobia is overcome. In this treatment, patients are not allowed to remove themselves from the situation [29]. The advantage of this approach is that it is quick and usually effective. The practice of flooding, also known as “immersion,” initially produces an anxious response of maximum intensity and, as a consequence of repeated exposure to the phobic stimulus, is subsequently followed by a physiological decrease. In reality, the subject tends to deliberately and consecutively avoid the confrontation with the anxiety-provoking stimulation, thus preventing the extinction of the phobic response. Through the flooding procedure, which is one of the so-called “strong” techniques of CBT, the therapist leads the patient through the experience, on an imaginative or real level, of the situation that scares the patient the most and for as long as possible. Generally, anxiety decreases after reaching a peak or, in some cases, disappears completely [30].

It is in this context that virtual reality treatments have been introduced. Virtual reality, or VR, is the simulation of a real situation with which a subject can interact using extremely sophisticated interfaces [31,32]. The technique can simulate flooding but with the use of advanced technology. As far as the technological aspect is concerned, VR consists of tools capable of acquiring information on the subject’s actions, which are integrated and updated by the computer in real time to build a dynamic three-dimensional world. Numerous studies have highlighted that VR can be a valid tool for CBT, allowing the patient to overcome certain obstacles, especially in the case of disorders whose treatment is based on “flooding” techniques with gradual immersive exposure, allowing experiences otherwise almost impossible, if not imaginatively (CBT-E). Using VR as a therapeutic tool has many advantages (CBT-VR). Therapy mediated by VR desensitizes the subjects from their anxieties, gradually accustoming them to emotions that they can try to manage through a different approach. Furthermore, the different components of the virtual environment are entirely under the control of the therapist, so as to allow him/her to establish, from time to time, the degree of difficulty to present to the patient. In this way, the therapist plays the role of mediator between the real and virtual world [33,34,35].

Several reviews and meta-analyses have considered VR as an adjuvant tool to exposure-based psychotherapy for the treatment of multiple anxiety disorders [34,35]. Virtual environments allow the psychotherapist to actively control multiple aspects of the stimuli presented and to identify parameters related to the dysfunctional response. These environments also guarantee the confidentiality and safety of patients. Numerous meta-analyses have shown that virtual environments evoke the same reactions and emotions as the situation experienced in the real world, that the sense of presence can also be experienced in environments characterized by a graphic realism that is not particularly accurate, and that they are strongly correlated with the possibility of interacting with the components of the virtual environment [34,35]. Many studies have used VR as a simulation, interaction, and distraction tool for patients with psychiatric illnesses such as PTSD, anxiety, specific phobia, schizophrenia, autism, and dementia. In this regard, VR environments offers a possibility of exposing patients to environments that can contribute to change patients’ emotions, cognitions, and behaviors and can thus be an important tool for psychiatric rehabilitation [35]. Nevertheless, there is a literature gap regarding the application of VR in the context of work-related stress disorders. Studies on this topic have focused on the application of VR in the workplace for stress management as a tool for relaxation and not as a technique of immersing oneself in a work stressful experience to promote a process of reorganization of cognitive schemas and emotional responses from the rehabilitation perspective [36]. 

Accordingly, we believe that it is important for occupational teams to explore this kind of application in the context of work-related stress disorders. The working community lacks standardized and proven rehabilitation protocols for workers affected by work-related stress disorders. 

The aim of this study is to evaluate the effectiveness of cognitive-behavioral training (CBT) with exposure to stressful work scenarios in imaginative (CBT-E) and in immersive virtual reality (CBT-VR) scenarios in a group of workers affected by work-related stress disorders and compare the clinical and physiological outcomes between the two exposure techniques. A long-term goal would be to develop an evidence-based rehabilitation program as a treatment for the reintegration into work of patients affected by these psychiatric disorders. In the future, a short, focused, and standardized rehabilitation process aimed at improving the symptoms of anxiety and depression could, in our opinion, contribute to globally reduce working days lost.

### 1.2. Study Hypotheses

Taking into consideration previous literature evidence where metanalyses [26,36] have underlined the greater effect of CBT on occupational stress both on psychological and physiological outcomes than other techniques as relaxation or organizational protocols, we expect a global positive influence of both CBT practices on workers’ mental health outcomes in term of a reduction of mood and anxiety symptoms, as well as a reduction of the physiological stress response (heart rate, respiratory rate, skin conductance, and body temperature) at the end of the whole training (Hypothesis 1). Nevertheless, the single term of the impact is unpredictable because the literature studies are very heterogenous. We hypothesize a greater efficacy from the CBT-VR because the rehabilitation program will be focused on imaginative techniques with gradual desensitization, and it is assumed that VR will allows a better immersive experience. In this regard, we predict greater levels of the physiological parameters during the first session of CBT-VR, as well as greater reduction during the last session with respect to CBT-E (Hypothesis 2). Further, regarding the future application of the method, we believe that work stress disease rehabilitation with CBT-VR could have a better impact in terms of the reduction of workdays lost in line with the improvement of clinical parameters and a better modulation of stress physiological parameters (Hypothesis 2). See Figure 1.

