### 2.5. Procedures, Outcomes, and Adverse Events

Participants will be randomized with a 1:1 ratio for CBT-E or CBT-VR without any specific criteria in order to prevent any randomization bias. Researchers involved in the outcome measures will be blinded to the allocation. Both the CBT training are assumed to be appropriate and beneficial for participants based on evidence from the literature. The training for each individual subject will begin within 7 days from T0, and each patient will perform 8 sessions of CBT-E/CBT-VR distributed 1 every week. If the subject is unable to perform the session on the scheduled day, a new date will be agreed within one week, failing which the patient would be excluded from the study. The intervention will also be discontinued if the participant withdraws consent or if a change in circumstance results in the participant meeting the trial exclusion criteria and becomes unsafe to engage in the intervention, or if any side effects would arise. These participants will remain in the analysis for data collected up until the date of withdrawal. The intervention is individualized, and progression/modification will be determined through discussions with the subject and the other members of the trial team. Every discontinuation will be replaced in order to reach the trial sample size.

The training protocol of CBT-E/CBT-VR is summarized in Table 5.

All outcomes will be performed before, during, and after the intervention phase, which is 10 weeks in total. The first week involves enrollment, randomization, and baseline data; the second to ninth week involves the training program; and the tenth week involves the patient final report. The outcomes measured will be physiological and clinical parameters, as well as their variations/comparison during the two training programs.

In particular, the physiological signs of stress reporting variations of temperature, skin conductance, heart rate, and respiratory rate will be recorded.

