**Figure 2 ijerph-20-05735-f002:**
[figure not shown]
Study procedures.

**Table 1 ijerph-20-05735-t001:** Gantt Chart.

Gantt Chart	Study Protocol Timeline							
	1–3 m	4–5 m	6–8 m	9–10 m T0 1st w	9–10 m 2–9 w CT	9–10 m T1 10th w	11–12 m	13 m
Protocol finalization								
Ethical and other reg. clearance								
Recruitment of sample for the CT								
CT intervention phase								
data collection								
Data analysis								
Dissemination								

**Table 2 ijerph-20-05735-t002:** Inclusion and exclusion criteria.

*Inclusion criteria*
Diagnosis of AD or PTSD according to the DSM-5 diagnostic criteria
Age ≥18 years
Being a worker
Good understanding of verbal and written Italian
Not having other Axis I diagnoses according to DSM-5 diagnostic criteria
Being drug-free for at least 2 weeks or on stable therapy for at least 12 weeks
Having signed the informed consent to participate in the study
*Exclusion criteria*
Severe cognitive impairment as to compromise the ability to understand the aims and characteristics of the study
Suicidal ideation, neurological, vestibular, or ocular disorders and other clinical entities in the acute phase
Having undergone any CBT training in the 6 months prior to the recruitment

**Table 3 ijerph-20-05735-t003:** Data collected from participants.

Demographic variables (age, gender, education level, civil status, children, family history of mental disorders, personal physical illnesses)
Work variables (field of work, public/private company, big/small company, type of contract, seniority level)
Physiological parameters (hearth rate, respiratory rate, temperature, and skin conductance)
Beck Depression Inventory-II (BDI-II), a 21-item self-report inventory measuring the severity of depression with two subscale (cognitive/affective and somatic) [19]
Self-rating Anxiety Scale (SAS), self-administered, 20-item tool for anxiety symptoms [37]
Job Content Questionnaire (JCQ), a self-administered workplace environment questionnaire to measure social and psychological characteristics of jobs with three main subscales (decision latitude, psychological job demands, and social support [9]
Pittsburgh Sleep Quality Index (PSQI), a self-rated questionnaire that assesses sleep quality and disturbances over a 1-month time interval [38]
Peritraumatic Distress Inventory (PDI), a 13-item self-report questionnaire that measures the level of distress experienced by an individual during and shortly after a traumatic event [39]

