Davidson Trauma Scale (DTS), self-rating for measuring the frequency and severity of Post-traumatic Stress Disorder (PTSD) symptoms in three clusters: intrusion/avoidance/hyperarousal [13]
Clinical Global Impressions Improvments (CGI-I), to quantify patient progress/treatment response over time [40]

**Table 4 ijerph-20-05735-t004:** Desktop application elements.

Setting selected in the initial menu
Gender of the character selected in the initial menu
Facial expressions selected in real time by keyboard
Body movements selected in real time by keyboard
Sentences in real time spoken by the operator and listened by the user with a voice that changes tone depending on the gender and personality of the character

**Table 5 ijerph-20-05735-t005:** CBT rehabilitation protocol for occupational stress diseases.

*Session 1*	Global evaluation of the patient. Administration of psychometric instruments. Assessment and engagement, including the development of a problem list and establishment of shared goals. Introduction to the principle of exposure therapy: definition and rationale.
*Session 2*	Classification of work stimuli through a Subjective Units of Distress Scale (SUDS: 0 = no anxiety at all; completely calm; 3 = some anxiety, but manageable: 5 = getting tough; wouldn’t want to have it all the time; 7–8 = severe anxiety that interferes with daily life; 10 = worst anxiety you’ve ever felt). Analysis of some sensations high distressed stimuli/situations avoided. Discussion of catastrophic interpretations. Disadvantages resulting from the avoidance and/or application of other dysfunctional behavioral mechanisms.
*Session 3*	Exposure to a neutral scene aimed at setting the exposition in the VR environment or in the imagination. Inter-session tasks: ABC techniques for work-related emotional stimuli. Practice of relaxing exercises.
*Session 4–8*	Exercises of exposure to the maximum phobic work stimuli, at the maximum level of intensity for an extended amount of time (flooding technique) using the VR environment or in imagination alternating with relaxation exercises. Analysis of the emotions felt during the approach to the phobic stimulus with re-elaboration of it and related thoughts. Identification of dysfunctional behaviors linked to it and identification of more functional behaviors.

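### Hypothesis 2 sets its physiological prediction at the first session, but Table 5 schedules no exposure then and no stressor before Session 4

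*Protocol article*

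**What the plan says.** Section 1.2 (Study Hypotheses) expects CBT-VR to be more effective because VR immerses the patient better, and then makes a specific prediction: "we predict greater levels of the physiological parameters during the first session of CBT-VR, as well as greater reduction during the last session", relative to CBT-E. A following sentence, also labelled Hypothesis 2, adds that CBT-VR "could have a better impact in terms of the reduction of workdays lost in line with the improvement of clinical parameters".

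Section 2.5 counts every weekly appointment as a treatment session: "each patient will perform 8 sessions of CBT-E/CBT-VR distributed 1 every week". Table 5 gives their content:

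- Session 1 is assessment, questionnaires, goal setting and "Introduction to the principle of exposure therapy: definition and rationale".
- Session 2 ranks and discusses stressful stimuli.
- Session 3 brings "Exposure to a neutral scene aimed at setting the exposition in the VR environment or in the imagination".
- Sessions 4 to 8 bring "Exercises of exposure to the maximum phobic work stimuli, at the maximum level of intensity for an extended amount of time", by VR or in imagination.

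Section 2.2 has physiological data recorded at T0, at every session and at T1. The work items in Table 3 are "Work variables (field of work, public/private company, big/small company, type of contract, seniority level". Section 2.5 names only physiological and clinical outcomes and ends the schedule at week 10.

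**The concern.** The prediction is about mechanism: VR should provoke a stronger stress response when exposure begins and a larger decline by the end of treatment. It can be tested only where the arms differ in exposure. By the numbering in section 2.5 and Table 5, the first session is one in which both arms receive the same content and nobody is exposed to anything. An analyst following the text would run a comparison that says nothing about immersion. If a Session 1 to Session 8 change were then taken, it would set a conversation against full exposure.

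If the authors mean the first exposure, the text does not say whether that is the neutral scene (Session 3) or the stressor (Session 4). The choice could then be made after the recordings have been seen.

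Two further points follow. The reduction is not defined, and one reading of it would favour VR for arithmetic reasons. Workdays lost appears under the hypothesis label with no variable listed to support it.

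**Working it through.** The plan gives no figure for the physiological prediction. Its one sample-size figure (26, for a 1-point CGI difference) plays no part here. The check is a comparison of sections plus short arithmetic.

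**1. Where the arms differ (Table 5)**

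| Session | CBT-VR | CBT-E | Do the arms differ? |
|---|---|---|---|
| 1 | assessment, rationale | same | no |
| 2 | ranking of stimuli | same | no |
| 3 | neutral scene in VR | neutral scene imagined | yes, no stressor |
| 4–8 | stressor in VR | stressor imagined | yes, with stressor |

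**2. Session 1 comparison as written**

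Inputs: significance level 0.05 (section 2.6), two-sided by assumption because sidedness is not stated; expected immersion effect 0 from step 1.

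- Chance of a significant result in the predicted direction = 0.05 / 2 = 0.025 per parameter. It does not depend on the number of patients.
- There are four parameters (heart rate, respiratory rate, skin conductance, temperature). Treating them as independent, which is an assumption, the chance that at least one is significant in the predicted direction = 1 − 0.975⁴ = 1 − 0.9037 = 0.096. In either direction it is 1 − 0.95⁴ = 0.185.

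**3. Openness of the wording**

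Three sessions could be called the first (1, 3 or 4). With four parameters that gives 3 × 4 = 12 candidate comparisons for the first half of the prediction alone.

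**4. What a between-session reduction would measure**

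Let d be the VR-minus-imagination difference at the first exposure and e the same difference at Session 8.

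Excess drop with VR = d − e.

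The documents give no value for d or e, so these heart-rate values are illustrative:

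| d (beats/min) | e (beats/min) | Excess drop with VR | End state with VR |
|---|---|---|---|
| 5 | 0 | 5 | equal |
| 10 | 0 | 10 | equal |
| 10 | 4 | 6 | worse by 4 |

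The first half of the prediction says d > 0. Whenever d exceeds e, the second half follows by subtraction, even if VR patients end no better or somewhat worse. This step applies only if the first session means the first exposure and the reduction is a drop between sessions. On the literal reading of step 2, the expected immersion component of d is zero and this problem does not arise.

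**5. Workdays lost**

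Table 3 lists no absence or sick-leave item, and section 2.5 lists no work outcome. Without a variable, a standard deviation and a time window, no power can be calculated.

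**The case against.** The strongest reply is that the meaning is clear from context. The prediction follows directly from the remark about immersion, so the first session most naturally means the first one delivered in VR. Since physiology is recorded at every session, the Session 3, 4 and 8 data will exist whatever the wording. That stands: no data are lost, and the correction is one of wording. It does not remove the conflict, because section 2.5 calls all eight appointments CBT-E/CBT-VR sessions, and the contextual reading still leaves Session 3 and Session 4 both possible.

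A second reply is that a reduction during the last session may be a fall within that session, in keeping with the Introduction's account of flooding as a peak response followed by a decline. That reading is open, and the arithmetic in step 4 would then not apply. This is why the plan should say which is meant, and why a reader should not infer that the contrast is biased toward VR as it stands. The text does not fix a between-session drop.

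A reader might also infer that Hypothesis 2 as a whole is untestable. The documents do not support that. Its leading claim, greater efficacy of CBT-VR, can be tested on the clinical scales in section 2.3.

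On workdays lost, a reader might infer that a trial endpoint has been left uncollected. The sentence is framed as a belief about future application and is hedged, and section 2.5 does not list it as an outcome. What remains is the hypothesis label.

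Finally, patients know their arm by Session 1, so anticipation could differ between arms. That would not be the immersion effect the hypothesis proposes.

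**Conclusion.** The concern holds for the physiological part of Hypothesis 2. Section 1.2 and Table 5 conflict: the session named has identical content in both arms, so a comparison there has an expected immersion effect of zero and would support the prediction 2.5% of the time per parameter by chance. This assumes a two-sided 5% test and that Session 1 runs as Table 5 describes.

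The warning about a larger drop arising from a higher start is conditional on the between-session reading. The workdays-lost point is secondary and concerns a label on a hedged expectation. The correction is worth making because it decides whether the mechanism claim is tested on informative recordings, but it threatens neither the clinical comparison nor the data to be collected.

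**What to change.** 1. Reconcile section 1.2 with Table 5 by naming the sessions compared: Session 4 (first exposure to the stressor) and Session 8 (last), optionally each relative to the Session 3 neutral scene in the same arm. This changes which recordings are analysed, not what happens in any session.
2. State whether the reduction is within Session 8 or between sessions. If it is between sessions, base any claim of better stress modulation on the Session 8 level or on the T0/T1 recordings already planned, not on the size of the drop alone.
3. Either take workdays lost out of Hypothesis 2 and leave it as a future aim, or add days absent from work over a stated window to the case report form.

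Items 1 and 2 cost a few sentences and no new data, since the sensors already record at T0, every session and T1. Item 3 costs a deletion or one added question. All should be settled before any physiological data are examined by arm.
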